#### Markers of cancer progression

Serum Prostate Specific Antigen (PSA) and cell-free DNA (cfDNA) will be measured to evaluate changes in markers of cancer progression. Serum PSA, in ng/mL, is measured as standard of care. Collected blood will be transferred to ARUP for analysis and data will be extracted from the medical record by the study team. Blood for cfDNA analysis will be collected in K2-ethylenediamine tetra-acetic acid anticoagulant collection tubes along with other study blood as described above. After collection, these samples will be transferred to HCI’s Biorepository and Molecular Pathology for processing. These samples will be centrifuged at 2,000 g for 10 min, with a brake speed of 7. Plasma will be aliquoted to cryovials and centrifuged once more at 1,500 g for 5 min. Samples will then be stored at -80^◦^C until batch analysis upon completion of data collection.

Upon completion of data collection, circulating cfDNA will be extracted using Maxwell® RSC 48 as per manufacturer’s specifications and using pre-designated kits per manufacturer, which include the Maxwell® CSC Whole Blood DNA Kit for genomic DNA and the Maxwell® RSC for circulating cfDNA. Extracted circulating cfDNA will then undergo quantity and quality check using Qubit 3.0 Fluorometer (Thermo Fisher Scientific, Waltham, MA, USA) and Bioanalyzer 2100 (Agilent Technologies, Santa Clara, CA, USA). For samples with severe genomic contamination from peripheral blood cells, a size selection will be performed with AMPure XP beads (Beckman Coulter, Brea, CA, USA) to remove large genomic fragments. Samples with a total yield < 5 ng will be considered inadequate for formal analysis or for downstream next generation sequencing methods.

### Statistical analysis

With respect to the primary outcome, we anticipate at least a 2 kg difference between intervention arms (Cr + RT vs. PLA + RT) in baseline to 52 week change in muscle mass based on sustaining, or more likely extending, differences seen in a supervised trial conducted by Chrusch and colleagues [56]. In this trial, 30 older men (mean age 70 + years) were randomized to Cr + RT vs. PLA + RT, and body composition and strength endpoints were compared at 12 weeks [56]. In the creatine arm, the men gained an average of 3.3 kg in muscle mass, while in the placebo arm, the men gained 1.3 kg, corresponding to a 2 kg difference in lean mass change over 12 weeks.

Muscle mass values within individuals are expected to be strongly correlated (after adjusting for time by treatment arm). In Chrusch and colleagues [56] study, repeated measurements of muscle mass over a short time interval, and without an intervening treatment, had an intra-subject correlation of 0.99. At each time point, the standard deviation of muscle mass was approximately 5.8. In our 12-week pilot study, we found a standard deviation of muscle mass of 8.24 kg with an intra-subject correlation between baseline and 12-week measurements of 0.975. We might realistically expect intra-subject correlation (ICC) of at least 0.85, given intervening treatment with RT and potentially creatine as well as a 52-week follow-up period. For a sample size of 200 (100 per arm), if the ICC is 0.85, then the power will be ∼ 84% for a mean difference of 2 kg muscle mass change.

The primary analyses will be conducted from a modified intention-to-treat perspective, with each subject analyzed according to their randomized study arm, irrespective of participation or compliance, as long as they complete their baseline assessments. Changes in muscle mass from baseline to 52-weeks will be compared between the Cr + RT and PLA + RT arms in the context of a linear mixed effects model, based on each subject’s measurements at baseline 24-weeks and 52-weeks, with a random effect for subject, and fixed effects for time, study arm, study arm by time interaction, and a priori anticipated important drivers of changes in muscle mass (age, length of time on ADT, ECOG performance status) at randomization. The effect estimate, and associated Wald test, of the study arm at 52 weeks corresponds to the estimate of the intervention effect (Cr + RT vs. PLA + RT), and its associated hypothesis test.

A few additional analyses are pre-planned to add robustness and clarity of interpretation. One suite of additional analyses will omit the 24-week follow-up measurements from the primary analysis model. Additional analyses will also be conducted omitting the anticipated drivers of responsiveness to intervention from the collection of adjustment variables. Lastly, we plan to conduct a suite a subgroup analyses, accompanied by subgroup by intervention arm interaction tests, for subgroups defined by age, length of time on ADT, baseline muscle mass, RT compliance (≥ 80% of scheduled sessions vs. <80%), and supplement compliance within the Cr + RT arm (≥ 80% of prescribed dose consumed vs. < 80%). Within the Cr + RT arm, compliance to creatine supplementation protocol will be summarized as percentage of prescribed doses overall and by phase (loading vs. maintenance phase), and changes in muscle mass from baseline to 52 and 24-weeks summarized separately for compliance groups (≥ 80% of prescribed dose vs. <80%, and ≥ 80% of scheduled sessions vs. <80%).

Analyses will assume that data is missing-at-random (MAR; data values are independent of the missing data mechanism conditional on the observed data), the most general data-centric missing data assumption [57]. Missing outcome data (e.g. muscle mass) will handled by simply omitting those observations from the mixed effects model, which is valid under MAR. Missing data on covariates (e.g., age, length of time on ADT, and ECOG performance status) will be handled via multiple imputation, which also ensures validity under MAR [58].

Notably, follow-up measurements missing due to patient death will not be MAR, and follow-up measurements missing due to severe declines in patient health may not be MAR either. Throughout, estimates for differences in baseline to follow-up changes in endpoints between the study arms will be conditional on the subset of patients who would have been able to continue on study procedures. While we do not anticipate enough overall survival or progression-free survival events for well-powered comparisons, these endpoints will be compared between study arms in supplemental analyses. Additionally, while we expect both study arms to provide benefits to our patients, the study will be under continuous oversight of an independent Data Safety Monitoring Committee at HCI, which will be monitoring for risks to patients.

Analyses for secondary endpoints (e.g., fatigue, physical function, cfDNA, etc.) will mirror the approaches described above for muscle mass. Additionally, we will examine relationships between changes in markers of cfDNA and PSA and changes in body composition, fatigue, strength, physical function, insulin sensitivity, and quality of life, at both 24 and 52-weeks. These relationships will be examined in the context of linear models adjusted for anticipated drivers of changes in endpoints such as baseline endpoint value, age, length of time on ADT, and ECOG, in the overall sample adjusted for study arm as well as separately for each study arm.

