## Methods

### Research design & participant population

#### Research design

This parallel, double-blind randomized controlled trial, that is 52-weeks in lengths, will randomly assign 200 mCSPC survivors receiving ADT to Cr + RT or PLA + RT with randomization in blocks of size four (two randomized to Cr + RT and two randomized to PLA + RT within each consecutive group of four subjects), stratified by age (< 70 years vs. ≥ 70 years) and ECOG performance status (0,1,2). To preserve the blind, only the Investigational Drug Services Pharmacy (IDS) personnel, the Research Compliance Office, and the Data Safety Monitoring Committee at Huntsman Cancer Institute (HCI) will know treatment assignments. Access to unblinded data/documents will be controlled by the pharmacy to ensure the blind is maintained. In the case of an emergency, [name] (mPIs) and the participant’s treating medical oncologist have the sole responsibility for determining if unblinding of a participant’s treatment assignment is warranted. If unblinding is warranted, the investigator will contact IDS for treatment assignment.

At baseline, completion of 24- and 52-weeks (end-of-study), we will assess muscle mass, fatigue, physical function, independence, insulin sensitivity, fat mass, and quality of life, and collect plasma for cell-free DNA analysis. We will also extract standard of care Prostate-Specific Antigen measurements from the medical record at these time points. All participants will be instructed to continue their typical diet and medication regimens. Figure 2 provides a schematic of the study design, intervention, and assessment time points. This study was approved by the University of Utah Institutional Review Board (IRB_00168125). The trial was registered in ClinicalTrials.gov (NCT06112990) on November 2, 2023 and is currently open to enrollment. Protocol amendments will be made as needed following standard procedures.

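### The stated power of about 84% for 100 per arm does not follow from the printed inputs, which give about 88% (minor, and conservative)

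*Protocol article*

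**What the plan says.** All the planning inputs are in the Statistical analysis section of the protocol article.

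- **Effect:** "we anticipate at least a 2 kg difference between intervention arms (Cr + RT vs. PLA + RT) in baseline to 52 week change in muscle mass".
- **SD, cited 12-week trial in older men:** "At each time point, the standard deviation of muscle mass was approximately 5.8". No unit is printed; I take it as kg.
- **SD, the team's own pilot:** "In our 12-week pilot study, we found a standard deviation of muscle mass of 8.24 kg".
- **Correlation:** "We might realistically expect intra-subject correlation (ICC) of at least 0.85".
- **Result:** "For a sample size of 200 (100 per arm), if the ICC is 0.85, then the power will be" about 84%, for a 2 kg difference in change.

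Allocation is equal (Research design): "two randomized to Cr + RT and two randomized to PLA + RT within each consecutive group of four subjects". The primary model is a linear mixed model on the baseline, 24-week and 52-week measurements, "with a random effect for subject, and fixed effects for time, study arm, study arm by time interaction". Missing outcome values are left out of that model under a missing-at-random assumption. The article gives no significance level, does not say which SD entered the calculation, and states no dropout rate.

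**The concern.** The power sentence attaches one figure to one sample size, one correlation and one difference. With either printed SD, the calculation at 100 per arm gives a different figure. This is a mismatch between printed numbers; it is not a complaint that detail was left to a fuller document.

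The figure matters because it is the only sample-size justification in the article. The patients have metastatic disease and are followed for 52 weeks, and the article itself expects some measurements to be lost through death or severe decline. A reader cannot tell whether the 84% is before or after such losses. A reader who takes it to be before losses, when it is in fact after them, would deduct dropout twice.

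**Working it through.** **Inputs.** Difference 2 kg; SD 8.24 kg or 5.8; correlation ρ = 0.85; 100 per arm (all from Statistical analysis). Two-sided 5% is my assumption.

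**Step 1: reproduce the stated figure with the pilot SD.**
- SD of change = SD × √(2(1 − ρ)) = 8.24 × √0.30 = 4.513 kg.
- Standard error = 4.513 × √(2/100) = 0.638 kg.
- 2 / 0.638 = 3.133.
- Power = Φ(3.133 − 1.960) = 88.0%; noncentral t gives 87.7%.

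With complete data, the 52-week change contrast in a random-intercept model has this same variance, so the planned model does not explain the gap.

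**Step 2: the other SD.** 5.8 × √0.30 = 3.177; standard error 0.449; 2 / 0.449 = 4.45; power 99.4% (noncentral t 99.3%).

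**Step 3: other methods at 100 per arm, SD 8.24, ρ = 0.85** (normal approximation).

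| Variant | Power |
|---|---|
| Change score, two-sided 5% | 88.0% |
| Baseline-adjusted, SD × √(1 − ρ²) = 4.341 | 90.3% |
| Mean of two follow-ups minus baseline | 95.1% |
| 52-week values only | 40.4% (68.4% with SD 5.8) |
| Change score, one-sided 5% | 93.2% |
| Change score, two-sided 2.5% | 81.4% |
| Change score, two-sided 1% | 71.2% |

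None comes within 2 points of 84%.

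**Step 4: what would give 84%.**
- With 100 per arm kept, one input has to move: ρ to about 0.83, SD to about 8.7 kg, two-sided alpha to about 0.032 to 0.034, or the difference to about 1.89 kg. The article prints none of these.
- With the inputs of step 1 kept and only the number changed:

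| Evaluable per arm | Normal | Noncentral t |
|---|---|---|
| 89 | 84.0% | 83.7% |
| 90 | 84.4% | 84.1% |
| 91 | 84.8% | 84.5% |
| 100 | 88.0% | 87.7% |

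**Step 5: tolerance to loss under the planned model.** The mixed model keeps the earlier measurements of patients who lack a 52-week scan. Let n = 100 per arm be randomized and m per arm have a 52-week value, with constant SD and correlation. The variance of mean change in one arm is then as follows.

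- *Others have baseline only:* SD² × [(1 − ρ²)/m + (1 − ρ)²/n]. For m = 79: 67.90 × (0.2775/79 + 0.0225/100) = 0.2538. Doubling and taking the root gives 0.712; 2 / 0.712 = 2.81; power 80.2%. At m = 78 it is 79.7%.
- *Others have baseline and 24 weeks:* put b = ρ/(1 + ρ) = 0.4595. The variance is SD² × [(1 − 2ρ²/(1 + ρ))/m + ((1 − b)² + b² − 2b(1 − b)ρ)/n]. For m = 75: 67.90 × (0.2189/75 + 0.0811/100) = 0.2532. The standard error is 0.712 and power 80.2%. At m = 74 it is 79.8%.

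With m = 100, both expressions reduce to SD² × 0.30/100, the variance in step 1.

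**The case against.** The strongest reply is that the calculation is underspecified, not wrong. The significance level and the choice of SD are mine, and a condensed article may leave both, with the attrition allowance, to a fuller document. That stands as far as the omissions go: I do not count any of them as a fault. It does not rescue the printed figure, because neither printed SD gives 84% at 100 per arm under any conventional significance level or analysis tried.

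A second reply is that four points matter little next to the uncertainty in the correlation. With SD 8.24 kg, a correlation of 0.83 gives about 83% and 0.90 about 97%, and the article offers 0.85 as a lower bound against 0.975 in its pilot. This also stands, and it is a reason to call the point minor.

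Three stronger readings may tempt a reader, and the article does not support them.

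- **That the sponsor built in a 10% loss.** The match at 89 to 91 per arm is suggestive, but it is a match to a rounded figure. Small shifts in the correlation, SD or alpha would also produce it, and no dropout rate is stated.
- **That the trial is underpowered.** At two-sided 5% the printed inputs give more power than is claimed.
- **That power falls below 80% beyond 19% loss.** That limit comes from a complete-case change score (81 per arm). The planned model uses partial data and holds 80% further.

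**Conclusion.** The point holds in a limited form. About 84% is not the power that the printed inputs give for 100 per arm. The figure is about 88% with SD 8.24 kg, a gap of about 4 points, and about 99% with SD 5.8. An unstated loss of about 10% is a possible explanation and no more than that.

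The conclusion rests on two-sided 5%, a change-score variance with correlation 0.85, and 5.8 being in kg. On those assumptions the error is conservative: no change in sample size, analysis or conduct follows. Under the planned mixed model, 80% power is held to roughly 21% missing at 52 weeks if those patients have baseline data only, and to roughly 25% if they also have 24-week data. Severity is minor.

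**What to change.** The sponsor should check its own calculation and then edit one sentence in one of two ways.

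1. If 100 analysed per arm was meant: correct the figure to about 88%, naming SD 8.24 kg, correlation 0.85 and two-sided 0.05.
2. If fewer evaluable participants were assumed: keep about 84%, attach it to that evaluable number per arm, and name the SD and significance level used.

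A 10% loss should be written in only if the sponsor's records show it was assumed. A statement that power is 80% at 19% loss should not be added, because it does not describe the planned model. If a tolerance is wanted, give the range of roughly 21% to 25% with its assumptions.

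The cost is one sentence, with no change to the sample size.

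### The primary model's listed covariates cancel out of the baseline-to-52-week contrast, so they adjust almost nothing and the planned analysis omitting them is not a real robustness check

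*Protocol article*

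**What the plan says.** All of the following is in the Statistical analysis section of the protocol article.

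- **Primary comparison.** "Changes in muscle mass from baseline to 52-weeks will be compared between the Cr + RT and PLA + RT arms".
- **Responses.** The linear mixed model uses each subject's "measurements at baseline 24-weeks and 52-weeks, with a random effect for subject". Baseline is therefore a response and not a covariate.
- **Fixed effects.** "fixed effects for time, study arm, study arm by time interaction", followed by "a priori anticipated important drivers of changes in muscle mass (age, length of time on ADT, ECOG performance status) at randomization". No covariate-by-time term and no common-baseline constraint is listed.
- **Reported effect.** "The effect estimate, and associated Wald test, of the study arm at 52 weeks".
- **Planned check.** "Additional analyses will also be conducted omitting the anticipated drivers of responsiveness to intervention from the collection of adjustment variables". It is one of several analyses offered as support for robustness.

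Secondary endpoints are to be analysed in the same way. By contrast, the linear models that relate changes in cfDNA and PSA to changes in other endpoints do adjust for the baseline value of the endpoint.

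**The concern.** The covariates are chosen because they are expected to drive change in muscle mass, so the evident purpose is to adjust the comparison of change. The listed terms do not do that: a time-constant covariate without a time interaction explains differences in level between patients, and those differences are already removed when baseline is subtracted.

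Three things are at stake.

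1. Readers would take the primary estimate as adjusted for length of time on ADT (which is not a stratification factor), age and ECOG, when in effect it is not.
2. Close agreement between the primary analysis and the omit-covariates analysis would be read as evidence of robustness, although the structure of the model nearly guarantees it.
3. Precision available from data already collected is left unused, both from covariates that may predict change and from the knowledge that randomized arms share a baseline mean.

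**Working it through.** **1. Algebra.** Write the listed model for subject i at visit j as

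Y_ij = b0 + t_j + a·A_i + d_j·A_i + g'X_i + u_i + e_ij,

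where A is arm, X holds age, ADT duration and ECOG, u is the subject effect, and t and d are zero at baseline. Subtracting baseline gives

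Y_i,52 − Y_i,0 = t_52 + d_52·A_i + (e_i,52 − e_i,0).

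The term g'X_i is gone, as are u_i and the free baseline arm difference a. With complete data the estimate of d_52 is the difference in mean change, whether or not X is in the model.

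**2. The plan's power figure.** Inputs from the Statistical analysis section: "we anticipate at least a 2 kg difference between intervention arms"; "we found a standard deviation of muscle mass of 8.24 kg with an intra-subject correlation between baseline and 12-week measurements of 0.975"; planning ICC 0.85; 100 per arm; stated power about 84%. Two-sided alpha 0.05 is assumed, because the article does not state it.

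- SD of change = 8.24 × √(2(1 − 0.85)) = 4.513 kg.
- SE = 4.513 × √(2/100) = 0.638 kg.
- Power = 88.0% by normal approximation, 87.7% by noncentral t.

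The stated 84% is not reproduced at 100 per arm. With 90 per arm it is 84.4% (84.1% by t), which would imply an unstated loss of about 10%. With the cited 12-week trial's SD of 5.8, power is 99.4%. This mismatch is a separate matter; the power figures below are shown at both sizes.

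**3. Effect of the covariates as listed.** Simulation: 500 trials per scenario, N = 200, SD 8.24, ICC 0.85, random-intercept REML. The share of change variance explained by the covariates (0, 10 or 20%) and the covariate-dependent dropout rates are assumptions. The article gives neither.

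| Dropout | Mean absolute shift in the 52-week change contrast, with vs without covariates | Largest shift | SE |
|---|---|---|---|
| none | 0.000 kg | 0.000 kg | 0.61-0.64 (approx.) |
| about 15% | 0.015-0.018 kg | 0.075 kg | 0.65-0.69 |
| about 30% | 0.021-0.024 kg | 0.12 kg | 0.71-0.75 |

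The zero in the first row holds even when the covariates explain 20% of the variance of change. Once covariate-by-time terms are added, the estimate does move: by 0.17-0.23 kg on average with complete data when the covariates explain 10-20% of change.

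**4. Precision from covariate-by-time terms** (complete data, empirical SD of the estimate, without and with the terms).

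- 0% of change explained: 0.649 to 0.654 (no gain).
- 10%: 0.652 to 0.621.
- 20%: 0.651 to 0.585.

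**5. Precision from a common baseline mean.** The variance per subject is 2·SD²(1 − ICC) for change and SD²(1 − ICC²) after baseline adjustment. The ratio is (1 + ICC)/2, so the saving is (1 − ICC)/2.

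- ICC 0.85: saving 0.15/2 = 7.5%; SD 4.513 to 4.341 kg; SE 0.638 to 0.614 kg. Power by t goes from 87.7% to 90.0% at 100 per arm, and from 84.1% to 86.7% at 90 per arm. In patients, 200 × 0.925 = 185 would give the same precision.
- ICC 0.975 (pilot, 12 weeks): saving 0.025/2 = 1.25%.

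The simulation agrees: in the 10% scenario with complete data the empirical SD fell from 0.652 to 0.626, a variance ratio of (0.626/0.652)² = 0.92.

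**The case against.** **The article is a condensed account.** It never says that the covariates enter as main effects only, and a fuller analysis plan, not shown, could add time interactions. That is fair as a limit on certainty. But the sentence is an explicit list of terms that names the one interaction it wants, so the point concerns what is stated and is not a complaint about missing detail.

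**The effect could be read as a level difference at 52 weeks.** The covariates would then matter: the estimate moves 0.25-0.35 kg, with an SE of about 1.2 kg. However, the same paragraph says that changes are compared. A comparison of levels alone would also have SE 8.24 × √(2/100) = 1.165 kg and power of about 40%, far from the stated 84%. The change reading is the better one, though the wording should be settled.

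**The two analyses are not strictly identical.** Correct. The article expects missing outcomes, and with dropout the mixed model also uses partial records. The differences are real but negligible against the SE.

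**A free baseline arm effect is legitimate.** It is valid under randomization, and the 7.5% is near the top of the range that the plan's own inputs support, since the ICC is put at 0.85 or more. This stands; the common baseline is an improvement and not the repair of an error.

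**Imbalance is limited.** Age (in two bands) and ECOG are stratification factors under Research design, so they are largely balanced. Chance imbalance in ADT duration is already reflected in the SE. This stands too.

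**Conclusion.** The point holds for the model as listed. Age, ADT duration and ECOG do not adjust the change contrast: the effect is nil with complete data, and about 0.02 kg on average at 15-30% dropout against an SE of about 0.7 kg. The analysis that omits them is close to uninformative about robustness.

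A reader might infer that the primary estimate is biased or the trial's conclusion invalid. The documents do not support that: with complete data, randomization keeps the estimate unbiased with or without these covariates. Bias through dropout would need dropout related to the covariates differently in the two arms, and covariates that strongly drive change; the article gives figures for neither. A reader might also infer a large, certain loss of precision. The common baseline is worth 7.5% of variance at ICC 0.85 (2-3 power points) and only 1.25% at 0.975, and the gain from covariate-by-time terms depends on how well the covariates predict change, which the article does not quantify.

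The conclusion rests on the literal term list, the change reading of the tested effect, two-sided alpha 0.05, and the assumed dropout and covariate effects in the simulation. It is a flaw of efficiency and of the sensitivity analysis, worth correcting before the analysis is fixed.

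**What to change.** 1. Add age-by-time, ADT-duration-by-time and ECOG-by-time terms to the primary model.
2. Constrain the arms to a common baseline mean. Equivalently in purpose, take the 24- and 52-week values as responses with baseline muscle mass-by-visit as a covariate.
3. State that the tested effect is the between-arm difference in baseline-to-52-week change.
4. Run the omit-covariates analysis against this model, so that it compares an adjusted with an unadjusted estimate.
5. Carry the same specification to the secondary endpoints that are to mirror the primary analysis.

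The cost is wording in the analysis plan and a few degrees of freedom. With age and ADT duration as single linear terms and ECOG in three levels, there are 1 + 1 + 2 = 4 covariate terms, times two follow-up visits, so 8 added parameters in 200 patients. If the covariates do not predict change, the result is a very slight loss of precision (0.649 to 0.654 in the simulation). No new data are needed.

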The addition of creatine monohydrate supplementation to an RT program can attenuate fatigue, the prominent barrier to RT among mCSPC survivors. Creatine is part of the phosphagen system and plays a critical role in energy metabolism [30]. Creatine monohydrate supplementation increases the availability of creatine and phosphocreatine in the skeletal muscle, which facilitates greater buffering of ATP and enhances exercise capacity and training volume, amplifying RT adaptations (Fig. 1) [30, 31]. Creatine monohydrate supplementation also reduces levels of inflammatory markers associated with severe muscle loss [6]. In addition, creatine monohydrate supplementation may have complementary effects to cancer treatment. Among preclinical models of varying cancer types, including prostate cancer, creatine and its analogs (e.g., cyclo-creatine) have exhibited the inhibition of tumor growth and proliferation [32–37]. In an 8-week trial comparing creatine supplementation to placebo among individuals living with stages III and IV colorectal cancer receiving chemotherapy, a significant increase in phase angle, a marker of body composition measured by bioelectrical impedance, was observed in the creatine group but not placebo [38]. Increases in phase angle indicate improved cellular integrity, permeability, and muscle mass, and have been linked with cancer survival [39, 40].

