#### Monitoring compliance to intervention procedures

Resistance training program compliance will be monitored and recorded in real time throughout each RT session. Additionally, study personnel will monitor compliance to the number of RT sessions completed per week. Participants will be provided and instructed to complete a daily supplementation log, and email this log to the study team weekly. If an email is not received, a member of the study team will call participants as a reminder to send the log or, if more convenient for the participant, verbally verify and record adherence to supplementation for that week. If a participant misses one week of RT for no given reason, or is non-adherent to the supplementation protocol, study personnel will call these individuals. Unused supplement containers will be returned to the HCI IDS Pharmacy at the 24-week and 52-week assessments for reconciliation.

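### Two compliance variables sit in the list for subgroup-by-arm interaction tests: one test cannot be estimated, and the other rests on a post-randomization split that can bias the arm comparison

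*Protocol article*

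**What the plan says.** In the protocol article, under Statistical analysis, the pre-planned additional analyses include a set of subgroup analyses "accompanied by subgroup by intervention arm interaction tests, for subgroups defined by age, length of time on ADT, baseline muscle mass, RT compliance" (split at 80% of scheduled sessions) and "supplement compliance within the Cr + RT arm" (split at 80% of prescribed dose). The clause on interaction tests governs the whole list, and neither compliance item is exempted. The next sentence separately plans summaries of muscle-mass change by compliance group within the creatine arm.

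Three other places bear on the point:

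- Under Monitoring compliance to intervention procedures, "study personnel will monitor compliance to the number of RT sessions completed per week", so RT compliance is built up during the 52 weeks. In the same section, "Participants will be provided and instructed to complete a daily supplementation log", and this applies to both arms.
- The Background states: "The addition of creatine monohydrate supplementation to an RT program can attenuate fatigue, the prominent barrier to RT among mCSPC survivors". It adds that creatine "enhances exercise capacity and training volume, amplifying RT adaptations".
- The primary analysis uses the randomized arm "irrespective of participation or compliance, as long as they complete their baseline assessments".

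**The concern.** The list mixes two kinds of variable. Age, time on ADT and baseline muscle mass are fixed before treatment, so within each level the arms are still comparable by randomization. The two compliance variables do not have that property.

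For supplement compliance, the subgroup is defined in one arm only. A subgroup-by-arm interaction compares the arm effect across subgroup levels, and with no placebo patients at either level there is no arm effect to compare.

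For RT compliance, the variable exists in both arms but is measured after randomization, and the protocol's own rationale gives a route by which creatine could change it. If creatine helps some less robust patients reach 80% of sessions, the creatine compliers include patients who would not have complied on placebo. The arm difference within a stratum then mixes the treatment effect with a difference in patient type.

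At stake is the reading of the additional analyses. One test would fail when run. The other would be reported beside genuine baseline subgroups with nothing to mark the difference.

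**Working it through.** The protocol gives no figure of its own for these subgroup tests, so there is none to reproduce. The checks below cover estimability and size.

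**1. Supplement compliance: can the interaction be estimated?**

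Code arm = 1 for Cr + RT and C = 1 for at least 80% of dose, with C defined only in Cr + RT and therefore 0 for every placebo patient. Then arm × C = C for all patients. The design [1, arm, C, arm × C] has two identical columns and rank 3 of 4. With three visits and all time terms the rank is 9 of 12. The interaction is not identified at any sample size. This step needs no assumptions.

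**2. RT compliance: how large could the distortion be?**

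Inputs from the Statistical analysis section: 100 per arm, 2 kg target difference, pilot SD 8.24 kg, intra-subject correlation 0.85. The SD of change follows:

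8.24 × √(2 × (1 − 0.85)) = 8.24 × √0.30 = 4.51 kg.

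Inputs that are assumptions, because the protocol gives no compliance rates:

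- A patient complies if 0.25 + 0.4 × arm + 0.8U + 0.6e > 0, where U is underlying health and U and e are independent standard normal.
- Change = 4.513 × (rU + √(1 − r²) × e₂), with e₂ also an independent standard normal, r = 0.3 or 0.5, and no arm effect.

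Since 0.8² + 0.6² = 1, the compliant share is Φ(0.25) = 0.599 on placebo and Φ(0.65) = 0.742 on creatine.

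Mean health in each stratum, with k = 0.25 (placebo) or 0.65 (creatine), φ(0.25) = 0.3867 and φ(0.65) = 0.3230:

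| Stratum | Formula | Placebo | Creatine | Difference |
|---|---|---|---|---|
| Compliers | 0.8 φ(k)/Φ(k) | 0.517 | 0.348 | −0.169 |
| Non-compliers | −0.8 φ(k)/(1 − Φ(k)) | −0.771 | −1.002 | −0.231 |

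Multiplying each difference by 4.513 × r gives the spurious arm difference when the true effect is zero:

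| r | Compliers | Non-compliers | Interaction (compliers minus non-compliers) |
|---|---|---|---|
| 0.3 | −0.23 kg | −0.31 kg | 0.08 kg |
| 0.5 | −0.38 kg | −0.52 kg | 0.14 kg |

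Against the 2 kg target, 0.23/2 is 11% and 0.52/2 is 26%. The overall arm comparison is unbiased by construction.

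**3. The same check with a true 2 kg effect in every patient**

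This is a large-sample simulation with change SD 4.51 kg. Here rho is the assumed correlation between the latent tendency to comply and the change in muscle mass.

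| Compliant, placebo vs creatine | rho | Compliers | Non-compliers |
|---|---|---|---|
| 70% vs 70% | 0.5 | 2.00 kg | 2.00 kg |
| 70% vs 80% | 0 | 2.01 kg | 2.00 kg |
| 70% vs 80% | 0.2 | 1.87 kg | 1.77 kg |
| 70% vs 80% | 0.5 | 1.67 kg | 1.47 kg |
| 60% vs 80% | 0.5 | 1.34 kg | 1.01 kg |

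The first two rows show that the bias disappears if the arm does not shift compliance or if compliance is unrelated to the change.

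**4. Size relative to sampling error**

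Under step 2, with about 60 and 74 compliers and 40 and 26 non-compliers:

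- SE in compliers = 4.513 × √(1/60 + 1/74) = 0.78 kg.
- SE in non-compliers = 4.513 × √(1/40 + 1/26) = 1.14 kg.
- SE of the interaction = √(0.78² + 1.14²) = 1.38 kg.

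A spurious interaction of 0.08 to 0.14 kg is 0.06 to 0.10 of its SE. It raises the false-positive rate of a 5% two-sided test to about 5.0 to 5.1%. The within-stratum biases are at most about half an SE (0.38/0.78 = 0.49; 0.52/1.14 = 0.46).

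**The case against.** The strongest reply has four parts.

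- **The interaction test is hardly disturbed.** The spurious differences have the same sign and similar size in both strata, so they largely cancel. This stands. The problem lies in the arm differences within strata, which a subgroup table would display, and much less in the test's error rate.
- **The bias is conditional.** The Background makes an effect of creatine on attendance plausible but gives no figure. Training volume is also not the same thing as sessions attended in a supervised programme. This stands too. A reader might infer that the RT-compliance comparison must be biased, or that it would manufacture a benefit for creatine. The documents support neither: both conditions in the working have to hold, and in the scenarios examined the distortion runs against creatine.
- **The supplement item may be loose wording.** Its restriction to one arm suggests a complier versus non-complier contrast within Cr + RT, which can be computed and which the next sentence describes. That is a fair guess at the intention. However, the descriptive summary is planned separately, and the text does not exempt the item from the interaction tests. Because both arms keep logs, a two-arm version could be built, but it would be another post-randomization split.
- **These are additional analyses.** The primary comparison ignores compliance. This is correct and limits the importance of the point.

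**Conclusion.** The point holds in a limited form. As written, the plan calls for one interaction test that cannot be estimated, whatever the data. It also treats RT compliance as if it were a baseline subgroup, although it is measured after randomization and the protocol's own rationale allows creatine to change it. Arm differences within RT-compliance strata are therefore not randomized comparisons.

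The sizes in the working are illustrations. They depend on assumed compliance rates and on an assumed link between health and muscle change, neither of which the protocol supplies. A reader might infer that the trial's main result is at risk. It is not, because the primary comparison does not use compliance.

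**What to change.** Restrict the subgroup-by-arm interaction tests to the three baseline factors: age, time on ADT and baseline muscle mass. Keep the summaries by compliance group that are already planned, and label them descriptive and non-randomized. Report RT compliance by arm as an outcome, which also speaks directly to the hypothesis that creatine helps patients train. This is a change of wording plus one simple comparison on data already being collected.

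Optionally, if the effect of actually taking creatine is of interest, add a complier-average estimate with randomized arm as the instrument and creatine consumed as the exposure, set to zero under placebo. State its assumptions: assignment affects muscle mass only through creatine consumed (the exclusion restriction), and the effect is linear in dose. Its cost is lower precision. It is not needed to repair the plan.
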